## 6.8 Lost to Follow-up

A participant will be considered lost to follow-up if they fail to return for at least one of the data collection visits and is unable to be contacted by study staff. The following actions must be taken if a participant fails to return to the clinics for a required study visit:

- The investigators will attempt to contact the participant and reschedule the missed visit within 2 weeks of the original schedule and counsel the participant on the importance of maintaining the assigned visit schedule and ascertain if the participant and their family wishes to and/or should continue in the study.
- Before a participant is deemed lost to follow-up, the investigator will make every effort to regain contact with the participant (where possible, 3 telephone calls and, if necessary, a letter or an email to be sent to the participant’s last known mailing address or email). These contact attempts will be documented in the participants’ study file.
- Should the participant continue to be unreachable, they will be considered to have withdrawn from the study with a primary reason of lost to follow-up.

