**Statistical Methods**

*Sample Size Calculation*

In the study regarding low dose atropine for myopia control, mean change in refractive error after one year was 0.64 ± 0.56D (mean ± SD) (10). Our previous randomized clinical trial showed DIMS slowed down myopia progression by approximately 60% (8). The sample size is calculated based on an assumption that, adopting atropine and DIMS together will result in a 60% reduction of mean refractive error change relative to using only atropine, the difference detected between two groups (atropine alone vs. atropine and DIMS) will be 0.384 (0.64 x 60% = 0.384), and the effect size will be 0.685 (0.384/0.56 = 0.685). According to power analysis (G*Power Version 3.1.9.2), 46 subjects are required per group to achieve 90% power with a significance level of 0.05 (two-tailed). Assuming the dropout rate will be 20%, 56 subjects will be required for each group in this proposal. Therefore, 112 subjects (56 subjects × 2 groups) will be required for the entire study.

As the quantitative effectiveness of DIMS combined with atropine is not known, two conservative assumptions are made during the sample size calculation: standard deviations are the same in the atropine plus DIMS group relative to the atropine alone group; and the previous study considering atropine tracked a 12-month change, while the proposed study treatment period will be 18 months.

*Statistical Analysis*

Data of right eyes will be used for analyses. Demographic and optometric data will be displayed as mean and standard deviation, or number and percentage as appropriate. The Chi-square test (or if appropriate Fisher’s Exact test) and unpaired t-test will be performed to compare baseline between-group differences in demographics (age, sex) and primary and secondary outcomes between the control group. Myopia progression over 18 months will be calculated as the difference between the primary outcomes (SER and AL) at the sixth and the first visits.

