## 6.7 Withdrawal Criteria

Participants (or parents / guardians for participants <18 years of age) are free to withdraw from participation in the study at any time upon request. No further data will be collected on participants who withdraw themselves from this study. If significant intolerance to study treatment is suspected at any time after randomization, participants may be requested to withdraw from the study at any time.

An investigator may discontinue or withdraw a participant from the study due to the following reasons:

- Significant study intervention noncompliance: unable to contact via three phone calls, more than three attempts to arrange missed follow-up appointments, wearing the spectacles less than five days a week and / or weekly average less than five hours/day.
- If any clinical adverse event or situation occurs (e.g. allergies to eye drops, reduction of visual function such as diplopia, reduction of BCVA; subject to clinicians’ judgement) such that continued participation in the study would not be in the best interest of the participant.
- If the participant meets an exclusion criterion (either newly developed or not previously recognized) that precludes further study participation.

Should participants require discontinuation of study treatment for any reason, or if they select to cease taking treatment, follow-up visits and data collection will not be continued as scheduled. The reason of discontinuation or withdrawal of participant from the study will be recorded on the Discontinuation / Withdrawal Case Report Form (CRF W) in Research Electronic Data Capture (REDCap). The use of REDCap can help reduce human errors in the randomization process, to assist data collection, and to provide a real-time dashboard for monitoring the project progress. Participants who sign the informed consent form, and are randomized but do not receive the study intervention may be replaced. If there are participants who signed the informed consent form, are randomized and received the study interventions but discontinue or withdraw within the first two weeks due to inability to meet inclusion criteria (e.g. unable to tolerate spectacles or eyedrops), and it is still within the recruitment period, then randomization of these participants will be discarded and replaced with a participant from the next allocation. All spectacles and eye drop (used or unused) will be returned to the investigator on withdrawal or discontinuation from the study.

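### Section 6.8 books an unreachable child as withdrawn after any one missed visit and provides no renewed invitation for the month-18 primary measurement

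*Combined protocol and SAP*

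**What the plan says.** Section 6.8 has a two-part trigger: a participant is "considered lost to follow-up if they fail to return for at least one of the data collection visits" and, as the same sentence goes on to require, staff cannot make contact. Staff first try to "reschedule the missed visit within 2 weeks of the original schedule", with counselling about later visits. Before the label is applied they must try to regain contact: "where possible, 3 telephone calls and, if necessary, a letter or an email to be sent". If that fails, "they will be considered to have withdrawn from the study with a primary reason of lost to follow-up". The section does not say which visits it means. Section 6.13.3 lists follow-up assessments at months 1, 6, 12 and 18.

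Section 6.7 covers part of the same ground. Among the reasons for which an investigator may withdraw a child, it counts as noncompliance "unable to contact via three phone calls, more than three attempts to arrange missed follow-up appointments". On withdrawal, spectacles and drops are to be returned.

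The Statistical Methods part of section 1 defines 18-month progression as the "difference between the primary outcomes (SER and AL) at the sixth and the first visits", that is, month 18 minus baseline. Section 7.2.4 replaces missing outcomes by multiple imputation (10 sets, missing at random), with complete-case and per-protocol sensitivity analyses. Section 7.2.3 tabulates premature discontinuations by arm and reason.

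**The concern.** Three of the four follow-up visits do not enter the primary change. Month 1 does not even include cycloplegic autorefraction or axial length (section 6.12). A family that misses one of these and is out of reach for a while has not lost its primary endpoint, but section 6.8 ends its place in the study. Nothing tells a site to try that family again when month 18 falls due, so a site following the text would not.

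An endpoint missing for this reason is imputed. Families know the lens type (section 6.6), so attendance could depend on arm or on perceived progression. Neither planned sensitivity analysis examines departures from missing at random, so a measured value is worth more than an imputed one.

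The overlap with section 6.7 adds a second problem: the same contact failure can be handled by two procedures and reported under two reasons in the by-arm table.

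**Working it through.** **1. The two sections side by side**

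| | Section 6.7 | Section 6.8 |
|---|---|---|
| Event | Three calls without contact, or more than three attempts to rebook | Missed visit and no contact |
| Letter or email | Not mentioned | If necessary, before the label is applied |
| Force | Investigator may withdraw | Listed actions must be taken |
| Reason recorded | Noncompliance | Lost to follow-up |

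The rebooking limb of 6.7 can also cover a family that answers the phone but keeps postponing. Such a family is not lost to follow-up under 6.8. Section 6.14 judges compliance by hours of spectacle wear and days of drops, neither of which is a contact measure.

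**2. The plan's sample size reproduced**

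Inputs from section 7.1: difference 0.384 D, SD 0.56 D, two-sided 5%, 90% power. Allocation is 1:1 (section 6.5).

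- Effect size d = 0.384 / 0.56 = 0.686.
- The two-sample t-test with noncentrality d × √(n/2) needs n = 45.7 per arm, rounded up to 46. This matches the plan. Power at 46 is 90.2%.
- The plan's 56 per arm equals 46 × 1.2 = 55.2, rounded up. Dividing by the retained fraction gives 46 / 0.8 = 57.5, rounded up to 58.
- With 20% loss from 56, 56 × 0.8 = 44.8 per arm remain, and power is 89.4%.

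**3. What recovered endpoints would be worth**

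The documents give no rate of interim contact failure or of later return, so only a range can be shown.

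| Evaluable per arm | Power |
|---|---|
| 42 | 87.4% |
| 45 | 89.6% |
| 46 | 90.2% |
| 48 | 91.4% |
| 50 | 92.4% |

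- Assumption A: 5% to 15% of 56 children per arm are unreachable around an interim visit, and half could be found by month 18. That is 56 × 0.05 × 0.5 = 1.4 to 56 × 0.15 × 0.5 = 4.2 endpoints per arm. Added to 44.8, this gives 46.2 to 49.0 evaluable, a range that lies between the rows for 46 and 50.
- Assumption B: a share of the planned 20% loss (56 × 0.2 = 11.2 per arm) is recovered. At 25%, 44.8 + 2.8 = 47.6 per arm (91.2%). At 50%, 44.8 + 5.6 = 50.4 per arm (92.6%).

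These figures count an unmeasured endpoint as contributing nothing. They concern refraction only, because the plan gives no power calculation for axial length.

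**The case against.** The strongest reply is that section 6.8 is milder than it may look, and much of that reply stands.

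- A reader might infer that one missed visit closes a child. It does not: failed contact is also required. A child who can be reached is counselled and rebooked.
- A reader might infer that the child is closed at two weeks. The two weeks are a target for rebooking. No deadline is set for declaring loss, and nothing says that a late month-18 measurement is disallowed.
- A reader might infer that these children are still on treatment. The documents do not show this. Drops are dispensed at visits (sections 6.3 and 6.12), the quantity per visit is not given, and a child who stays away may run out. Spectacle wear could continue.
- A reader might infer that primary data are certain to be lost. In section 6.7 the bar on further data covers participants who withdraw themselves, and the separate stop covers those who discontinue treatment. Neither expressly forbids measuring an unreachable child who comes back.
- Ordinary loss is already in the 20% allowance, and nothing shows loss beyond it. A link between unreachability, arm and outcome is possible but not demonstrated.
- Section 6.7 is permissive and 6.8 mandatory, so 6.7 need not displace the 6.8 steps. A distorted table of reasons is a risk, not a finding.

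What remains is that 6.8 assigns withdrawn status without regard to which visit was missed and provides no later attempt. Saying that such children are unreachable anyway does not fully answer this, since failed contact around month 6 says little about month 18, and the rebooking limb of 6.7 can reach families who are in contact.

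**Conclusion.** The point holds as a minor one with a cheap remedy. The plan does not separate a missed interim visit from loss of the month-18 endpoint, so some primary values may be imputed that could have been measured. Sections 6.7 and 6.8 give contact failure two thresholds and two reason codes. Both statements rest on the text alone.

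The size of the gain is unknown. Three more evaluable children per arm, from 45 to 48, are worth 91.4% − 89.6% = 1.8 percentage points of power on the plan's own difference and SD. It would be wrong to conclude that the trial is underpowered because of this rule. The better reason to act is that measured endpoints reduce reliance on an untested missing-at-random assumption in a trial where families are unmasked. The explicit stop on data collection after treatment discontinuation in section 6.7 is a separate and more direct route to missing data. Correcting it would leave section 6.8 unchanged.

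**What to change.** In section 6.8:

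- Record a missed interim visit as a missed visit.
- Unless consent has been withdrawn, attempt contact again for each later visit, including month 18.
- Assign final lost-to-follow-up status for the primary outcome only after the month-18 attempt has failed.
- Measure any child who returns, including late, and record the actual date.

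Interim visits keep their place, since they supply secondary outcomes, adverse-event data and tolerability checks.

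Reconcile section 6.7 with 6.8 so that contact failure has one procedure and one reason code. Which grounds for discontinuation to retain is for the sponsor and investigators to settle.

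The cost is a few sentences of protocol wording, some additional calls, and some month-18 measurements taken off schedule.

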## 6.9 Eligibility and Baseline Assessment

All data will be collected via face-to-face meetings with researchers at The University of Hong Kong and Optometry Research Clinic of School of Optometry from The Hong Kong Polytechnic University. The following data will be collected at the baseline and eligibility assessment according to the manual of procedures.

- **Demographic data:** Ethnicity, age (date of birth) and gender.
- **Concomitant medication:** Information about types and dose of medications currently used (will be asked at all visits).
- **Allergies history:** Information about any allergies to medication or others (will be asked at all visits).
- **Health history:** Information about any previous ocular surgery and current or previous health problems related to vision or visual development.
- **Daily schedule:** Bedtime and wake up time.
- **Questionnaire:** Information about the history of myopia of the participants.
- **Visual acuity:** For best corrected VA, distance visual acuity will be measured using the highly standardized ETDRS letter chart adopted by the Amblyopia Treatment Study group (20), while habitual and subjective refraction VA will be measured by letters in Thomson Test Chart 2000 system. Near visual acuity will be measured using the LogMAR modified ETDRS near visual acuity letter chart.
- **Presence of strabismus:** Measured using the cover test.
- **Autorefraction and keratometry:** Measured using Shin-Nippon NVision-K 5001 open-field autorefractor. Five measurements will be taken and averaged only for autorefraction.
- **Pupil size:** Measured in photopic and mesopic lighting conditions using NeurOptics VIP-300 pupillometer.
- **Subjective refraction:** Measured by trial frame and trial lenses (maximum plus before blur) for sphere, Jackson cross cylinder for astigmatism and Thomson Test Chart 2000 system for VA.
- **Binocular vision with best subjective refraction:** Stereopsis is measured by Randot Stereotest, monocular and binocular amplitude of accommodation is measured by RAF rule, binocular accommodative lag is measured with 0D, 2D, 3D, 4D and 5D stimuli by Shin-Nippon NVision-K 5001 open-field autorefractor, and phoria is measured using Howell Phoria Card, or using cover test in the eligibility assessment. Five measurements will be taken and averaged only for binocular accommodative lag.
- **Colour vision**: Measured by Ishihara Test.
- **Intraocular pressure:** Measured by Topcon CT-80 Non-contact Computerised Tonometer.
- **Choroidal thickness:** Measured by Heidelberg Spectralis HRA+OCT with enhanced depth imaging mode (optical coherence tomography) or Topcon Triton Swept Source OCT.
- **External ocular health examination:** examined using a slit lamp biomicroscope.
- **Cycloplegia:** One drop of proxymetacaine 0.5% or Provain-POS 0.5% (topical anaesthetic) and 1 drop of cyclopentolate HCL 1.0% (antimuscarinic eye drop) will be instilled to both eyes to induce cycloplegia. Information sheet about drug will be distributed before performing cycloplegia, listing the drug name, effective ingredients, effective time, duration and side effects. The effect of the cycloplegia will be evaluated by means of amplitude of accommodation (push-up method) measured by RAF rule; if the amplitude of accommodation is more than +2.00D, then a second drop of cyclopentolate 1.0% will be instilled to both eyes. The remaining tests of this section will be performed under cycloplegia.
- **Cycloplegic autorefraction:** Same procedures as non-cycloplegic autorefraction. Five measurements will be taken and averaged.
- **Peripheral refraction:** Measured by Shin-Nippon NVision-K 5001 autorefractor at centre, 10˚, 20˚ and 30˚ of the nasal and temporal visual field across the horizontal meridian in both eyes. Five measurements will be taken and averaged.
- **Cycloplegic subjective refraction:** Same procedures as non-cycloplegic subjective refraction.
- **Axial length:** Measured by IOL Master 500 (Carl Zeiss) (partial coherence interferometry). Five measurements will be taken and averaged.
- **Ocular biometry:** Corneal curvature, corneal thickness, anterior chamber depth, lens thickness and axial length will be measured using Lenstar LS900 (optical low coherence reflectometry). Five measurements will be taken and averaged only for axial length.
- **Posterior ocular health examination:** examined using a binocular indirect ophthalmoscope and fundus photo (Topcon TRC-NW8 Fundus Camera).

## 6.10 Primary Outcome Measure

The primary outcome measures are changes in cycloplegic refraction in spherical equivalent and axial length over 18 months from baseline, as measured by cycloplegic autorefraction (Shin-Nippon open-field autorefractor) in both eyes and by IOL Master 500 (Carl Zeiss) respectively.

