**Criteria for Evaluation**

*Primary outcomes*

The primary outcome measures are changes in cycloplegic refraction in spherical equivalent and axial length over 18 months from baseline.

*Secondary outcomes*

The secondary outcome measures are accommodative amplitude and response, pupil size, other ocular biometrics, treatment compliance, and adverse events and intervention events at all visits.

Other optometric outcomes not listed here will be considered exploratory in nature.

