# 7. Statistical Considerations

## 7.1 Sample Size

In the study regarding low dose atropine for myopia control, mean change in refractive error after one year was 0.64 ± 0.56D (mean ± SD) (10). Our previous randomized clinical trial showed DIMS slowed down myopia progression by approximately 60% (8). The sample size is calculated based on an assumption that, adopting atropine and DIMS together will result in a 60% reduction of mean refractive error change relative to using only atropine, the difference detected between two groups (atropine alone vs. atropine and DIMS) will be 0.384 (0.64 x 60% = 0.384), and the effect size will be 0.685 (0.384/0.56 = 0.685). According to power analysis (G*Power Version 3.1.9.2), 46 subjects are required per group to achieve 90% power with a significance level of 0.05 (two-tailed). Assuming the dropout rate will be 20%, 56 subjects will be required for each group in this proposal. Therefore, 112 subjects (56 subjects × 2 groups) will be required for the entire study.

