## 7.2 Statistical analysis

Statistical analyses will be performed using SPSS. Data of right eyes will be used for analyses. Data from the trial will be entered into an excel spreadsheet and extracted into a statistical program for analysis. Data analyses will be specified *a priori* in a statistical analysis plan (SAP) prepared by the researchers (and agreed upon by all members of the Steering Committee). All statistical tests will be two-tailed and a 5% significance level maintained throughout the analyses.

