### 7.2.2 Treatment effects

The effectiveness of myopic control will be calculated as:

1 – (progression therapy) / (progression control)

Unpaired t-test will be used to compare the changes in primary outcomes between two groups. If statistically significant differences in baseline demographic characteristics between groups are found, these significant covariates will also be adjusted in these primary analyses with Analysis of Covariates. In this case, both the unadjusted and adjusted results will be reported. Multiple regression analysis with the primary outcomes at the final visit will act as the dependent variable and independent variables, alongside with the secondary outcomes, will be employed to identify factors that may associate with myopia control effectiveness.

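### Primary SER is described as measured in both eyes but only right eyes are analysed: state one eye rule throughout, and consider averaging the eyes for a small gain in precision

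*Combined protocol and SAP*

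**What the plan says.** Section 6.10 is where the primary outcomes are tied to instruments: the changes are "as measured by cycloplegic autorefraction (Shin-Nippon open-field autorefractor) in both eyes and by IOL Master 500 (Carl Zeiss) respectively". As the sentence is built, the reference to both eyes belongs to the autorefraction, and axial length has no eye attached. The axial length entry in Section 6.9 is also silent: "Measured by IOL Master 500 (Carl Zeiss) (partial coherence interferometry). Five measurements will be taken and averaged". The peripheral refraction entry in the same list does specify both eyes.

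The Overview (Criteria for Evaluation) says "The primary outcome measures are changes in cycloplegic refraction in spherical equivalent and axial length over 18 months from baseline" and names no eye. The registration items in Section 2 name none either.

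The analysis text is definite. Section 7.2 says "Data of right eyes will be used for analyses", and the Overview's Statistical Analysis paragraph repeats the sentence. Section 7.2.2 adds: "Unpaired t-test will be used to compare the changes in primary outcomes between two groups". The sample size in Section 7.1 counts children, which fits one value per child.

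No section says how two eyes would be combined or what left-eye SER is for. The sensitivity analyses in Section 7.2.4 are complete-case and per-protocol only. Section 6.1 requires qualifying myopia in both eyes.

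**The concern.** Someone who goes to Section 6.10 for the endpoint finds SER from both eyes. Someone who goes to Section 7.2 finds an analysis of one eye. Neither section refers to the other, and the eye for axial length must be inferred from the general right-eye sentence. A primary outcome and its analysis rule should match without inference.

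There is also a small efficiency question. Both eyes must be myopic to enter, and the spectacles under comparison are worn over both, so the left eye should carry the same treatment contrast. Section 6.10 says its SER is measured. Leaving it out gives up some precision that would cost no further SER measurement.

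**Working it through.** **Inputs from Section 7.1:** control mean change 0.64 D, SD 0.56 D (a one-year figure); difference 0.64 × 0.60 = 0.384 D; two-sided alpha 0.05; 46 per group for 90% power.

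**Assumptions, not in the documents:** between-eye correlation of change ρ from 0.70 to 0.95; equal SD and equal treatment effect in the two eyes; 0.56 D is the SD for one eye. Section 7.1 does not say whether that SD comes from one eye or from an average.

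**Step 1: reproduce the plan's figure.** d = 0.384/0.56 = 0.686. For a two-sample t-test with n per group, the noncentrality is d√(n/2) on 2n − 2 degrees of freedom. At n = 46 this is 0.686 × √23 = 3.29 on 90 degrees of freedom, and power is 90.2%. At n = 45 power is 89.6%. The required number is therefore 46, as stated, and one eye per child meets the target.

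**Step 2: variance of the child mean.** With SD σ in each eye, Var[(R + L)/2] = (σ² + σ² + 2ρσ²)/4 = σ²(1 + ρ)/2. The SD of the two-eye mean is therefore 0.56 × √((1 + ρ)/2).

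**Step 3: put this SD into the same t-test.**

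| Analysis | SD (D) | d | Variance saved | n per group for 90% | Power at 46 per group |
|---|---|---|---|---|---|
| Right eye only | 0.560 | 0.686 | none | 46 | 90.2% |
| Two-eye mean, ρ = 0.95 | 0.553 | 0.694 | 2.5% | 45 | 90.9% |
| Two-eye mean, ρ = 0.90 | 0.546 | 0.704 | 5% | 44 | 91.6% |
| Two-eye mean, ρ = 0.80 | 0.531 | 0.723 | 10% | 42 | 92.9% |
| Two-eye mean, ρ = 0.70 | 0.516 | 0.744 | 15% | 39 | 94.2% |

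In other terms, the second eye adds 2/(1 + ρ) − 1 of an observation per child, from 0.03 (ρ = 0.95) to 0.18 (ρ = 0.70). The confidence interval narrows by a factor of √((1 + ρ)/2), that is 0.99 to 0.92.

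**Step 4: validity of the test.** The child mean is one value per child, so the unpaired t-test and the conditional ANCOVA in Section 7.2.2 need no change. Entering the two eyes as separate, independent values would be wrong. The test statistic's variance would be inflated by 1 + ρ, and the nominal 5% error would become 2[1 − Φ(1.96/√(1 + ρ))], or 13.3% at ρ = 0.70 and 16.0% at ρ = 0.95.

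**The case against.** The best defence is that the plan is coherent as it stands. The words about both eyes sit inside a description of how SER is measured, and Section 6.9 uses the same phrase that way for peripheral refraction. The analysis eye is fixed in advance, unconditionally and identically in two places. Analysing one pre-specified eye is an accepted way to avoid within-child correlation, and the t-test and sample size fit it. This stands, and it limits the point to a clarification and an optional gain.

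It also rules out four stronger readings that a reader might infer:

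- **That the endpoint has two rival definitions and either could be reported as primary.** No section plans a two-eye or left-eye analysis, and the right-eye sentence leaves no choice open. Right-eye and two-eye results would sometimes fall on different sides of p = 0.05, as any two correlated estimators do. That would matter only if the eye could be chosen after seeing the data.
- **That half the primary data are thrown away.** This is at most a count of SER readings. In information the loss is 2.5% to 15% of variance under the assumed correlations.
- **That left-eye axial length is available at no cost.** The documents do not say that the IOL Master is used on both eyes.
- **That the right-eye rule pulls power below 90%.** It does not. The 56 per group matches 46 × 1.2 = 55.2 rounded up, and 20% dropout from 56 leaves 44.8, with 89.6% power at 45. That shortfall comes from the dropout inflation and is a separate matter.

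What the defence does not answer is that 6.10 should name the analysed eye for both outcomes, and that left-eye SER has no stated purpose.

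**Conclusion.** The point holds as a cheap improvement. The outcome section refers to both eyes for SER and to no eye for axial length, while the analysis sections use right eyes. The right-eye analysis is valid and adequately sized at 46 per group. A two-eye mean would raise power at that number from 90.2% to between 91.6% and 94.2% for ρ of 0.9 to 0.7, and only to 90.9% if ρ is 0.95.

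The size of the gain rests on the assumed correlation and on 0.56 D being a per-eye SD. If 0.56 D already described an average of two eyes, the right-eye SD would be larger and 46 per group slightly too few for the right-eye rule. The existence of a gain needs only similar SDs and treatment effects in the two eyes and a correlation below 1. No figure can be given for axial length, because the documents supply neither an SD nor a statement that both eyes are measured for it.

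**What to change.** State one eye rule, in the same words, in Section 6.10, Section 7.2 and the Overview, and carry it into the SAP that Section 7.2 says will be prepared. Do this before outcome data are examined.

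- **Preferred rule:** the primary SER outcome is each child's mean of right- and left-eye change in cycloplegic autorefraction from baseline to month 18. Treat axial length the same way if the sponsor confirms that the IOL Master is used on both eyes; otherwise name the right eye for it explicitly.
- **Sensitivity analysis:** keep the right-eye analysis, so that results can be compared with right-eye-only publications.
- **One eye unreadable:** say in advance whether the readable eye's value stands for the child or the other eye is imputed. The multiple imputation in Section 7.2.4 could take this in.
- **Minimum alternative:** if the sponsor keeps right eyes as primary, add a clause to 6.10 saying that SER is measured in both eyes and that the right eye is analysed for both outcomes, with the two-eye mean as a sensitivity analysis.

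The cost is a wording change and one derived variable per outcome, with no extra children and no extra SER measurement. The downsides are the need for the one-eye-missing rule and reliance on the sensitivity analysis for comparison with right-eye-only publications.
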